### Exploratory outcomes

Exploratory outcomes include anthropometric measures, such as waist circumference measured between the iliac crest and lowest rib, blood pressure measured on the right upper arm after 10 min of rest in a sitting position, resting heart rate after 10 min of rest, HDL, LDL cholesterol, blood glucose, triglycerides, blood insulin, HOMA index, and Framingham score.

Moreover, the severity of psychiatric symptomatology (as evaluated at the BPRS) and the levels of cognitive dysfunctions (as evaluated at the brief-MATRICS) were considered exploratory outcomes.

## Baseline assessments

At baseline the following socio-demographic information were collected: age, gender, marital status, level of education, working condition, economic status, number of family members, illness duration, time in charge at the mental health center (months), number of (voluntary and involuntary) hospitalizations, suicide attempts (numbers). Moreover, ECG evaluation was mandatory in order to check the eligibility to perform moderate physical activity.

## Statistical analyses

### Sample size and power calculation

A power analysis has been implemented in order to define the sample size needed to detect a significant BMI reduction (primary study's outcome) between the two groups. In particular, it has been estimated a sample size needed to observe a mean difference between the two groups of at least one point at the BMI (kg/m^2^) (with standard deviation of 2), with power set at 90% and a significant two-tailed alpha level of 0.05, based on previous studies on the same topic [e.g., (21, 23)].

Taking into account the multicenter design of the study, sample size has been adjusted for the Intercluster Correlation Coefficient (ICC), set at 0.030, and for the coefficient of variation of cluster sizes (COV), set at 0.400 (55). Therefore, the sample size consists of 348 patients (29 patients per arm in each center). Each center is expected to recruit 58 patients, rounded to 60. Moreover, previous trials evaluating the efficacy of interventions focused on physical activities and diet reported a drop-out rate of 15%; thus, the sample size has been rounded to 35 patients per arm for each center. Therefore, the expected sample size consists of 420 patients (70 patients for each participating center). This sample size has been considered feasible by all participating centers (Figure 1).

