### Patients' recruitment

Patients are being recruited in six outpatient units from the universities of Naples, Bari, Genova, L'Aquila, Pisa, and Rome—Tor Vergata.

Eligible patients are identified by their clinicians and referred to the LIFESTYLE research staff by phone, email, or in-person contact. After the patients have been contacted, a meeting is arranged at the outpatient clinic with the referring clinician and the LIFESTYLE staff. Verbal and written information about the project are provided. If the patient accepts to participate to the study, an informed consent form is signed and an appointment for baseline assessment is made. Once the informed consent is collected, the patient is formally enrolled in the study's protocol. Before starting the baseline assessment, the LIFESTYLE staff member contacts the statistician working at the Coordinating Center for obtaining the randomization code for patients' group allocation. The randomization procedure is stratified according to center, age, gender, and educational level with a 1:1 ratio. The treating psychiatrist will continue to provide the usual treatment to patients.

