The intervention lasts 5 months and it is administered to groups of 5–10 patients every 7–10 days. The sessions cover the following topics: (1) healthy diet; (2) physical activity; (3) smoking habits; (4) medication adherence; (5) risky behaviors; (6) promotion of circadian rhythms. Each module includes the following components: (a) information on the risks of the specific unhealthy lifestyle and benefits in adopting healthy lifestyle; (b) teaching of practical strategies to change unhealthy behaviors; (c) identification of personal life goals for each participant, motivation to change, and problem-solving strategies. Sessions have been developed in order to stimulate discussion, work-groups and interaction among participants. At the end of each meeting, a 20-min session of moderate physical activity is scheduled (Table 1). The core feature of this intervention is the inclusion of the motivational component. During each session, group participants are supported by mental health professional in identifying a personal healthy lifestyle goal. After goal-definition, professionals help participant to define the motivations for lifestyle changing and teach problem-solving strategies for sustaining the behavioral change.

**Table 1 T1:** Programme of LIFESTYLE psychosocial group intervention.

Starting session: Introduction of the intervention, aims, purposes, presentation of participants, and definition of personal healthy lifestyle goals
Module 1: Diet, information on health food, principles, and benefits of healthy eating
Module 2: Physical activity, how to increase routine physical activity
Module 3: Smoking habits, information on the dangers of smoking, craving, difficulties for quitting smoking and consequences of long-term abuse of nicotine.
Module 4: Medication adherence, strategies for improving adherence, medical consequences of non-adherence
Module 5: Risky behaviors, sexually transmitted disorders, substance, and alcohol abuse
Module 6: Promotion of regular circadian rhythm, problems related to irregular daily activities
At the end of each meeting, a 20-min session of moderate physical activity (i.e., walking) is implemented with participants

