### Arm II: brief educational group intervention

The brief educational group intervention, which includes elements from the psychoeducational approach and from problem-solving techniques, consists of 5 weekly sessions and it is administered to groups of 5–10 patients. The following topics are covered: (1) healthy lifestyle; (2) early detection of clinical relapses; (3) effects of pharmacological treatment and management of side effects; (4) stress management techniques; (5) problem-solving techniques.

Manuals have been developed in order to ensure treatment fidelity among the different centers. Leaflets and other written materials are given to patients, whenever relevant. During the sessions, interaction among participants is supported using role-plays and work-groups (Table 2).

**Table 2 T2:** Programme of LIFESTYLE educational brief group intervention.

Starting session: Introduction of the intervention, aims, purposes, and presentation of participants
Module 1: Healthy lifestyle (e.g., healthy diet, physical activity, smoking habits, promotion of circadian rhythm)
Module 2: Early detection of psychiatric relapses
Module 3: Pharmacological treatment and management of side effects
Module 4: Stress management techniques
Module 5: Problem-solving techniques
Information and leaflets are provided to participants during each session. Positive changes are highlighted, potential strategies for change are discussed at each module. The main aim is to provide patients with the principles of healthy living (i.e., eating fruit and vegetable, drinking water, doing moderate physical activities, not abusing of alcohol, quit smoking, etc.)

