The implementation of a generalized estimated equation model (GEE). The GEE provides an estimation of the longitudinal impact of the interventions on primary and secondary outcomes, controlling for confounders, such as physical comorbidities, severity of psychiatric symptoms, level of social functioning, quality of life, self-esteem, recovery style, support from social network. A generalized estimating equation model will be employed using the following outcomes variables: the BMI, the severity index of the Cumulative Illness Rating Scale, the abdominal circumference: plasma levels of glucose, insulin, triglycerides, and cholesterol levels (total, LDL, and HDL); systolic and diastolic blood pressure, and cigarettes smoked per day.The development of a Structural Equation Model (SEM) in order to identify possible mediators and moderators of the efficacy of the interventions, controlling for several confounders such as age, gender, severity of symptoms, BMI, etc. In particular, the variable “duration of the intervention” will be tested as one of the most relevant mediator or moderator for the efficacy of the interventions.The implementation of multivariable logistic regression models, in order to identify predictors of positive response for changing unhealthy behaviors. In particular, as regards the primary outcome, this will be transformed in binary variable (yes vs. no) using the reduction of at least 1 point at the BMI as threshold. The impact of possible predictors (e.g., having an healthy diet; walking at least 30min per day; quitting smoking) as well as confounders (such as age, gender, level of education, diagnosis, duration of the illness, type of pharmacological treatment received) will be tested in a logistic regression model.A subgroups analysis, according to the different diagnostic groups, in order to identify different profiles of efficacy of the interventions. The hypothesis is that patients suffering from affective disorders (both major depression and bipolar disorders) will report a higher improvement in the reduction of BMI and in changing their unhealthy lifestyle behaviors compared to patients with schizophrenia.

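### The sample size is inflated for centre clustering although patients are randomised within centre, while clustering by therapy group is in neither the sample size nor the GEE as described; power is understated, not short.

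*Protocol article*

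**What the plan says.** In the Protocol article, Sample size and power calculation targets a "mean difference between the two groups of at least one point at the BMI", with SD 2, "with power set at 90% and a significant two-tailed alpha level of 0.05". It then adds a clustering adjustment: "Taking into account the multicenter design of the study, sample size has been adjusted for the Intercluster Correlation Coefficient (ICC), set at 0.030", together with a coefficient of variation of cluster size of 0.400. This leads to 348 patients (29 per arm in each of six centres), and to 420 (35 per arm per centre) after 15% drop-out. The only reason given for the adjustment is that the study is multicentre.

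Patients' recruitment says of allocation: "The randomization procedure is stratified according to center, age, gender, and educational level with a 1:1 ratio". Every centre therefore contributes patients to both arms.

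Both interventions are delivered in groups. For Arm I, "it is administered to groups of 5–10 patients every 7–10 days"; Arm II "consists of 5 weekly sessions and it is administered to groups of 5–10 patients".

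Data analysis describes the model this way: "The GEE provides an estimation of the longitudinal impact of the interventions on primary and secondary outcomes". It lists patient-level confounders as examples. It names no cluster unit, and mentions neither centre nor therapy group.

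**The concern.** A design effect for centres belongs to a trial that randomises whole centres. Here the centre is a stratum with both arms inside it, so anything the two arms of a centre share drops out of the treatment contrast. The adjustment is thus made at a level that does not match the design.

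The therapy group is different. Each group sits wholly in one arm, and its members share sessions and, in Arm I, physical activity after each meeting. Correlation of BMI outcomes within groups would not cancel between arms. If it exists and the analysis treats patients as independent, standard errors are too small and the false-positive rate exceeds 5%. The GEE is planned for BMI and several other outcomes, so the issue could reach beyond the primary comparison.

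**Working it through.** **Inputs from the protocol article.** Difference 1, SD 2, power 90%, two-sided alpha 0.05, ICC 0.030, COV 0.400, six centres, 348 evaluable, 15% drop-out, 420 enrolled, therapy groups of 5–10.

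**Assumptions, not in the document.** Therapy-group ICC 0.01–0.10, the same in both arms; coefficient of variation of group size 0.2; normal approximation.

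**Step 1: reproduce 348.** Without clustering, n per arm = 2(1.960 + 1.282)² × 2²/1² = 84.06, so 85. With unequal clusters, DE = 1 + [(1 + COV²)m − 1] × ICC.

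- Centre-by-arm cell as cluster, m = 29: DE = 1 + (1.16 × 29 − 1) × 0.030 = 1.979. Then 85 × 1.979 = 168.2 per arm; divided by 6 this is 28.04 per cell, rounded up to 29; 29 × 12 = 348.
- Whole centre as cluster, m = 58: DE = 1 + (1.16 × 58 − 1) × 0.030 = 2.988; 170 × 2.988 = 508. This is not 348.
- Drop-out: 29/0.85 = 34.1, rounded up to 35; 35 × 12 = 420.

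The plan's figure is therefore that of a parallel cluster trial with six clusters per arm.

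**Step 2: power with randomisation inside centre.** With centre in the model, the variance factor is about 1 − ICC = 0.97, not 1.98. With 420 × 0.85 = 357 completers (178 per arm) and no group clustering, ignoring even the small gain from the 0.97:

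power = Φ(1/(2√(2/178)) − 1.96) = 99.7%.

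**Step 3: add therapy-group clustering.** DE = 1 + [(1 + 0.2²)m − 1] × ICC, and

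- power = Φ(1/(2√(2·DE/178)) − 1.96)
- difference detectable at 90% power = (1.960 + 1.282) × 2 × √(2·DE/178)
- true type I error if groups are ignored = 2[1 − Φ(1.96/√DE)]
- narrowing of the confidence interval if groups are ignored = 1 − 1/√DE

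| Group size | ICC | DE | Power | Detectable difference | Type I error if ignored | CI too narrow by |
|---|---|---|---|---|---|---|
| 5 | 0.01 | 1.042 | 99.6% | 0.70 | 5.5% | 2% |
| 5 | 0.03 | 1.126 | 99.4% | 0.73 | 6.5% | 6% |
| 5 | 0.10 | 1.420 | 97.7% | 0.82 | 10% | 16% |
| 7.5 | 0.01 | 1.068 | 99.5% | 0.71 | 5.8% | 3% |
| 7.5 | 0.03 | 1.204 | 99.0% | 0.75 | 7.4% | 9% |
| 7.5 | 0.10 | 1.680 | 95.3% | 0.89 | 13% | 23% |
| 10 | 0.01 | 1.094 | 99.5% | 0.72 | 6.1% | 4% |
| 10 | 0.03 | 1.282 | 98.6% | 0.78 | 8.3% | 12% |
| 10 | 0.10 | 1.940 | 92.3% | 0.96 | 16% | 28% |

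**Step 4: when would power fall below 90%?** When DE exceeds 178/84.06 = 2.118. That needs a group ICC above about 0.27 (groups of 5), 0.16 (7.5) or 0.12 (10).

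**The case against.** **The analysis half rests on silence.** The article names no cluster unit, working correlation or variance estimator, its confounder list is open-ended, and a separate analysis plan may settle all of this. That stands. Reading the longitudinal GEE as clustered on patient alone is the natural reading but not a stated fact. Nor does the article say that therapy-group membership goes unrecorded.

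**The power half does no harm.** This also stands. A reader might infer from a wrong 90% that the trial is too small. The documents do not support that: the unneeded centre factor (1.98) exceeds every group design effect in the table (at most 1.94), so the error leaves spare power. Data analysis also plans intention-to-treat with last observation carried forward, so the analysed set may be larger than the 357 used here; that only raises the power.

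**Some inflation may be defensible.** Only the part of the centre effect common to both arms cancels. If the treatment effect varies between centres, that variation remains, and a calculation on 12 cells would allow for it. The section does not give that reason. Facilitators may also cancel in part: Training of mental health professionals says each centre's three professionals were trained to provide both interventions, and who leads which group is not stated.

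**The size depends on an assumed ICC.** It does. At ICC 0.01 the type I error is only 5.5–6.1%, and an outcome with no group correlation is not affected at all.

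None of this rescues the sample size paragraph, which states an adjustment and a reason that do not fit randomisation within centre.

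**Conclusion.** The point holds in two parts of different strength.

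First, as written, the sample size is adjusted for the wrong level of clustering. This follows from the article's own figures and needs no assumption about ICCs. The stated 90% is not the power of this design, and it errs on the low side.

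Second, the clustering that group delivery can create is absent from both the power calculation and the GEE as described. A reader might conclude that the planned confidence intervals and tests are simply wrong, for BMI and every secondary outcome. The documents do not go that far. The inflation in the table's last two columns arises only if the GEE clusters on patient alone and the outcome has a positive group ICC.

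This should be corrected, but it does not threaten the adequacy of 420 patients.

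**What to change.** - **Sample size paragraph:** keep 420. Replace the centre design effect with a therapy-group design effect (size 5–10, ICC 0.01–0.10), and restate either the power (about 92–99.6%) or the difference detectable at 90% power (about 0.70–0.96 BMI points). Alternatively, justify the present factor explicitly as an allowance for arm-by-centre variation.
- **Data:** make sure a therapy-group ID is held for every patient in both arms. Without it, no later model can allow for the groups.
- **Primary model:** make the therapy group the clustering unit of the GEE, with a small-sample correction (420/10 = 42 to 420/5 = 84 groups), or fit a mixed model with random effects for group and patient. Enter centre as a fixed effect.

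The cost is at most one extra data field, revised wording, and somewhat wider confidence intervals where group correlation exists. No more patients are needed.

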**Figure 1 F1:**
[figure not shown]
Power analysis and sample size.

### Data analysis

Statistical analyses will be conducted according to the “Intention To Treat” principle. Missing data will be handled using the Last Observation Carried Forward (LOCF). All patients who signed informed consent form as well as those who undergo the initial assessment will be included. Descriptive statistics will be calculated for the dependant and confounding variables for both groups. The homogeneity of the two groups for these variables at baseline will be checked. In all cases, a bilateral alpha of 0.05 is considered an error and confidence intervals are calculated at 95%.

The analytic plan includes:

The implementation of a generalized estimated equation model (GEE). The GEE provides an estimation of the longitudinal impact of the interventions on primary and secondary outcomes, controlling for confounders, such as physical comorbidities, severity of psychiatric symptoms, level of social functioning, quality of life, self-esteem, recovery style, support from social network. A generalized estimating equation model will be employed using the following outcomes variables: the BMI, the severity index of the Cumulative Illness Rating Scale, the abdominal circumference: plasma levels of glucose, insulin, triglycerides, and cholesterol levels (total, LDL, and HDL); systolic and diastolic blood pressure, and cigarettes smoked per day.The development of a Structural Equation Model (SEM) in order to identify possible mediators and moderators of the efficacy of the interventions, controlling for several confounders such as age, gender, severity of symptoms, BMI, etc. In particular, the variable “duration of the intervention” will be tested as one of the most relevant mediator or moderator for the efficacy of the interventions.The implementation of multivariable logistic regression models, in order to identify predictors of positive response for changing unhealthy behaviors. In particular, as regards the primary outcome, this will be transformed in binary variable (yes vs. no) using the reduction of at least 1 point at the BMI as threshold. The impact of possible predictors (e.g., having an healthy diet; walking at least 30min per day; quitting smoking) as well as confounders (such as age, gender, level of education, diagnosis, duration of the illness, type of pharmacological treatment received) will be tested in a logistic regression model.A subgroups analysis, according to the different diagnostic groups, in order to identify different profiles of efficacy of the interventions. The hypothesis is that patients suffering from affective disorders (both major depression and bipolar disorders) will report a higher improvement in the reduction of BMI and in changing their unhealthy lifestyle behaviors compared to patients with schizophrenia.

All data will be collected and analyzed by a statistician, who will be blinded during the trial. Data will be stored in hard copy by each center in a safe place. They will be placed on an online dataset, and will be accessible to each unit. For each patient, only the recognition ID will be reported in the dataset. For safety reasons and to ensure patients' privacy, the dataset will be protected by a password. Each center will have its own password, and will be responsible for data entry. A statistician from the coordinating center will manage data collection and will provide assistance to researchers in case of difficulties in using the software. It will be possible to export data in compatible formats with common calculation software (e.g., Microsoft Access and Excel) and in specific software (e.g., SPSS, STATA) for statistical analyses.

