## Assessment time and instruments

Researchers participating to the study are blinded to patient allocation. All patients are assessed at the following time points: baseline (T0); 2 months post-randomization (T1); 4 months post-randomization (T2); 6 months post-randomization (T3); 12 months post-randomization (T4); and 24 months post-randomization (T5). T1 and T2 assessments include only anthropometric tests. All data will be collected through a paper and pencil interviewing and the expected time for filling in all assessment tools is about 60/90 min. During the completion of the assessment battery, whether patients feel distressed or exhausted, the assessment can be stopped and another appointment will be scheduled in the next 2/3 days with the researcher.

The following questionnaires and schedules will be used during the study (Table 3):

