## Anticipated results

### Primary outcome

BMI has been selected as primary outcome since it is a reliable and feasible anthropometric parameter, and it has already been considered in previous studies on lifestyle interventions (15, 16, 24). The primary outcome is the change of the BMI at 6 months post-randomization (T3). We expect a mean difference between the two groups of at least one point (and standard deviation of 2 points) at BMI. The work hypothesis is that the LIFESTYLE psychosocial group intervention will be more effective than the brief educational group intervention in reducing the BMI.

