In this study, we aim to evaluate the cost-effectiveness of the interventions, since only Verhaeghe et al. (79) found that the intervention is cost-effective only in men with a significant BMI reduction. For improving the dissemination of psychosocial interventions targeted on healthy lifestyle behaviors, it is necessary to prove that these interventions are cost-saving. In order to improve feasibility of the interventions in the clinical routine care, we decided not to include dieticians or physical trainers, since the involvement of health professionals different from psychiatrists or psychologists could hamper the dissemination of the interventions in the routine practice. Of course, this hypothesis should be further tested in multicentric studies involving different European countries, since it could be that workload and multidisciplinary staffs include different health professional according to the organization of the National health care. At least in Italy, the inclusion of specific health professionals such as dieticians and physical trainers is not the routine for the mental health care. A critical element in our research protocol is the attrition rate from the two intervention groups. As already pointed out in other studies on lifestyle psychosocial interventions, such as the CHANGE (22, 23) and CAPICOR (21) trials, the attrition rate ranges from 5 to 40% and we expect an attrition rate of at least 15%. Nevertheless, in order to guarantee attendance, patients will continue to be in contact with their referring clinicians during the provision of the intervention, and will receive phone or e-mail reminders for each session of the intervention. Moreover, the active involvement of patients as “experts” could further motivate them to attend the sessions during the intervention. This project represents the first multicentric randomized head-to-head comparison trial for evaluating the efficacy of psychosocial interventions targeting unhealthy lifestyle in people with severe mental disorders in Italy. In particular, we aim to test the efficacy of two different interventions targeting lifestyle behaviors. In particular, considering that one of the main critical issue is related to the optimal duration of the interventions, this aspect will be evaluated in our trial since we will test the impact of the “duration of the intervention”, as one of the possible mediator or moderator of the efficacy of the interventions.

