The trial has some limitations, which must be acknowledged. A first limitation is the selection bias of patients accepting to participate to the LIFESTYLE trial. In fact, it could be that only highly motivated patients accept to take part to the study and will continue to attend all scheduled sessions. Another possible limitation is the use of manuals for clinicians carrying out the intervention. While this methodological choice was made in order to increase external validity and reliability of the interventions, it may have limited the generalizability of the intervention to other patients. Moreover, the two interventions are different in terms of frequency of contact with the mental health professionals. This aspect will be considered as a potential confounder for the effectiveness of the intervention. Finally, another possible limitation of the study is the global duration of the intervention. In fact, Naslund et al. (80) recently highlighted that lifestyle interventions of ≥12-months duration appear to be more effective compared to those lasting ≤6-months. Moreover, other studies have found a modest or small effect for short-term interventions, suggesting that longer interventions should be studied. On the other hand, long approaches are associated with a higher drop-out rate of patients who may have difficulties in attending structured long-term approaches (81–84). Therefore, we will explore the efficacy and the effectiveness of a medium-term intervention with multiple follow-up assessments.

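### LOCF as the only missing-data method can bias the 6-month BMI contrast and sets early dropouts to zero change on the questionnaire outcomes

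*Protocol article*

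**What the plan says.** The Data analysis section opens with "Statistical analyses will be conducted according to the “Intention To Treat” principle" and continues with "Missing data will be handled using the Last Observation Carried Forward (LOCF"). Everyone who consented or had the initial assessment is to be included. The LOCF sentence names no outcome or visit to which it is confined, and nothing else in the article replaces or supplements it.

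The other statements that bear on it are:

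- Primary outcome section: "The primary outcome is the change of the BMI at 6 months post-randomization (T3"). The sample size section plans to detect "a mean difference between the two groups of at least one point at the BMI", with a standard deviation of 2.
- Data analysis section, on the model: "The GEE provides an estimation of the longitudinal impact of the interventions on primary and secondary outcomes".
- Assessment time and instruments: "T1 and T2 assessments include only anthropometric tests". Table 3 agrees: BMI is recorded at T0, T1, T2, T3, T4 and T5, but the questionnaires only at T0, T3, T4 and T5.
- Interventions: Arm I runs for 5 months and Arm II for 5 weekly sessions.
- Discussion, on earlier lifestyle trials and this one: "the attrition rate ranges from 5 to 40% and we expect an attrition rate of at least 15" per cent. In the limitations: "long approaches are associated with a higher drop-out rate of patients who may have difficulties in attending structured long-term approaches".

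**The concern.** LOCF is an assumption about what happens to patients after they leave: that nothing changes. The trial is built on the expectation that BMI does change between T0 and T3, and it expects a sizeable minority to be missing at T3. Three things follow.

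1. The primary contrast can be biased, and the direction depends on the BMI trend and on which arm loses more patients. LOCF is therefore not reliably conservative.
2. For outcomes without T1 and T2 measurements, the only value available to carry to T3 is baseline, so every earlier dropout is scored as exactly zero change. In the planned responder analysis (a fall of at least 1 BMI point), a patient with only a baseline BMI is a non-responder by construction.
3. At T4 and T5, which serve the long-term aim, part of the reported result would be an earlier measurement under a later label. A patient last seen at baseline contributes a value 24 months old at T5.

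Carried values also enter the GEE as if observed, so the analysis does not reflect the uncertainty due to missing data.

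**Working it through.** **How the plan itself treats dropout.** The sample size can be reproduced from its stated inputs (difference 1, SD 2, 90% power, two-sided alpha 0.05, ICC 0.030, coefficient of variation 0.400, six centres, 15% dropout).

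- Per arm without clustering: 2 × (1.960 + 1.282)² × 2² / 1² = 84.1, so 85.
- Design effect at 29 per arm per centre: 1 + [(1 + 0.4²) × 29 − 1] × 0.03 = 1.979.
- 85 × 1.979 = 168.2 per arm; 168.2 / 6 = 28.04, so 29; 12 × 29 = 348, as stated.
- Dropout: 29 / 0.85 = 34.1, so 35; 12 × 35 = 420, as stated.

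The inflation treats dropouts as supplying no T3 value. LOCF then analyses all 210 per arm, of whom about 0.15 × 210 = 31.5 would have a carried value.

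**LOCF mean at T3.** Assumptions that are not in the article: BMI changes linearly to a total of *e* at T3; a fraction *d* drops out, with the last visit equally often T0, T1 or T2 (months 0, 2, 4); dropouts would have continued on the same line.

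LOCF mean = (1 − d)e + (d/3)(0 + e/3 + 2e/3) = e(1 − 2d/3)

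**True difference of 1 point, Arm I loses 1, Arm II flat.** Because Arm II is flat, only Arm I dropout matters. The last column is the variant in which every dropout has baseline as the last value, with mean e(1 − d).

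| Arm I dropout | LOCF difference, spread dropout | LOCF difference, baseline carried |
|---|---|---|
| 15% | 1 − 0.10 = 0.90 | 0.85 |
| 25% | 1 − 0.167 = 0.83 | 0.75 |
| 40% | 1 − 0.267 = 0.73 | 0.60 |

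With equal dropout in both arms, the true difference is multiplied by (1 − 2d/3) whatever the control trend, so 15% always gives 0.90.

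**No true difference, both arms change by e.** The LOCF difference (Arm I minus Arm II; negative favours Arm I) is (2/3) × e × (d₂ − d₁).

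- Equal dropout: 0.
- 25% vs 5%, both lose 1 point: (2/3)(−1)(−0.20) = +0.13.
- 40% vs 5%, both lose 1 point: (2/3)(−1)(−0.35) = +0.23, against the long arm.
- 40% vs 5%, both gain 0.5: (2/3)(0.5)(−0.35) = −0.12, in favour of the long arm.

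The arm splits are hypothetical. The 40% vs 5% case takes the two ends of a range reported across earlier trials and is an extreme, not a forecast.

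**The other pattern.** If dropouts stop changing on the day they leave, the true T3 mean under intention to treat is itself e(1 − 2d/3). LOCF then has no bias, and 0.73 at 40% is the truth. If dropouts who had lost weight regain it, LOCF overstates the benefit.

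**The case against.** The strongest reply is that every bias figure rests on dropouts continuing to change after they leave. A patient who leaves Arm I straight after baseline is credited with the full 1-point loss. That is only one scenario. If change stops at dropout, LOCF is right, an available-case analysis would give about 1.00, and a missing-at-random mixed model would also tend to overstate the effect. This stands: the figures illustrate what can happen and do not measure what will. But LOCF has no better claim, because the article does not justify the assumption that change stops.

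A second reply is that the planned case is mild. At 15% equal dropout the loss is 0.10 BMI points against an SD of 2; it is toward the null and creates no false positive. This also stands.

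Two stronger readings are tempting and are not supported:

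- A reader might infer that the article documents higher dropout in Arm I. It gives no dropout by arm. The limitations sentence follows a contrast of programmes of 12 months or more with those of 6 months or less, and the article calls its own intervention medium-term. That sentence concerns attending the programme, whereas all patients in both arms are scheduled for assessment. Unequal loss is plausible given 5 months against 5 weekly sessions, but its size is unknown.
- A reader might infer that the standard errors are shown to be too small. In a simulation (210 per arm, SD 2, 15% dropout independent of outcome, clustering ignored) the standard error was 0.186 with LOCF and 0.212 for available cases. These are different estimators, and the effect shrinks too: 0.90 / 0.186 = 4.84 against 1.00 / 0.212 = 4.72. The raised type I error seen in the simulation came from bias under unequal dropout. What can be said is that single imputation does not represent the uncertainty about the missing values.

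**Conclusion.** The point holds. The article fixes LOCF as the only missing-data method, so this is not a detail left to an analysis plan that is not shown. Its effect on the primary estimate runs from none (change stops at dropout, or no true effect with equal dropout) to a loss of 0.10 to 0.27 of a true 1-point difference at 15% to 40% attrition in the long arm, under continued linear change and evenly spread dropout. A false difference under no effect needs unequal dropout; its sign follows the BMI trend and the arm with more loss. Confidence is high that the method is poorly chosen, and lower on the size of the bias. The consequences for questionnaire outcomes at T3 and for carried values at T4 and T5 follow directly from the visit schedule, without any assumption about the size or arm split of dropout.

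**What to change.** In the Data analysis section, replace LOCF as the primary method with an analysis that uses all observed BMI values from T0 to T3. Either of these would do:

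- a likelihood-based mixed model for repeated measures, or
- multiple imputation by arm, using baseline, T1 and T2 BMI, followed by the planned GEE. Simply running an unweighted GEE on the observed data is not enough, since it needs data missing completely at random.

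Apply the same principle to the secondary outcomes and to T4 and T5. Because both options assume missing at random, which fails if change stops or reverses at dropout, add one sensitivity analysis for data missing not at random (delta-adjusted or reference-based).

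The cost is revised wording, a little more programming and a somewhat larger reported standard error. The T0, T1 and T2 BMI values are already collected, and the sample size of 420, which already allows for 15% loss, does not change.
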